#### Data collection

2.3.3

Consenting participants will be emailed a link before the baseline call to complete the pre- and poststudy surveys in the REDCap secure database. Daily diaries will be returned using a stamped, self-addressed envelope to the investigative team. With regard to qualitative data, semistructured interviews will be conducted in person or through videoconference call by a member of the research team using a pre-established set of questions (see Table 2) that cover the following areas: perceptions of VRGM, perceived benefits of VRGM, whether and how VRGM has impacted pain severity and interference with function, perception of pain and previous mindfulness meditation experience (42), and factors underlying satisfaction and dissatisfaction with study participation. Participants who drop out of the study will also be invited to participate in the semistructured interview. Interviews will be audio-recorded, and recordings will be transcribed verbatim.

**Table 2 T2:** Semistructured interview script.

• Please describe your experience in the virtual reality guided mindfulness program. Was there anything outstanding for you? • Were the mindfulness techniques that you used or learned through virtual reality helpful for your pain? If so, could you please describe them and explain how they related to your day-to-day pain symptoms? • Please describe your experiences of doing virtual reality guided meditation at home. Were there strategies that you used to help with home practice? If so, could you please describe them and explain how you applied them? • Do you have any suggestions for how to improve participant experience in future studies?

### Intervention

2.4

Consistent with previous similar studies (33, 43), the VRGM intervention will consist of a 10–15 min, once-daily session for 6 weeks. The VR headset will present a range of preinstalled 3D high-quality calming virtual environments (i.e., nature scenes and sounds), such as mountain meadows, white sands, spring creek, and other beautiful nature scenery (e.g., beaches, waterfalls, and tall trees). The headset includes a motion tracker that measures the position of the head and adjusts the visual image accordingly, which can make participants feel as if they can look around and move through the virtual environment. Built-in speakers on the VR headset will provide an audio narrative of guided mindfulness practice.

The content of the audio is based on the research team's previous work with the evidence-based mindfulness-based cancer recovery program (17) and will include instructions to perform weekly mindfulness exercises (one exercise per day) for 6 weeks (see Table 3). Each meditation exercise has its own unique preinstalled virtual environment, selected on the basis of which was best suited for each type of meditation. All virtual environments will also be customized to synchronize with the meditation audio (e.g., mixing movement with sound).

**Table 3 T3:** Virtual reality-guided mindfulness for pain curriculum.

Day	Teaching (∼5 min; first 2 days only; can be listened to repeatedly or skipped after week 1)	Guided meditation practice (∼10–15 min)	Virtual reality experience
1	Introduction: What is mindfulness?	Awareness of breath	White sands
2	Awareness of pain	Body scan	Waterfall cliffs
3	N/A^a^	Awareness of pain	Misty summit
4	N/A	Loving kindness	Spring creek
5	N/A	Mini breathing exercises	Oceanview
6	N/A	Mountain meditation	Mountain meadows
7	N/A	Healing from pain	Forest stream

^a^
N/A, not applicable.

### VR hardware specifications

2.5

The Pico Neo 3 Pro (PN3P) is a 6 degrees of freedom standalone VR headset with a high resolution 4k liquid crystal display (1,832 × 1,920 pixels per eye) and 90 Hz refresh rate (44). The PN3P was released in May 2021 and retailed for $699 USD. It accommodates for a wide range of different eye features, as the user is able to adjust the lens spacing at three settings (58 mm, 63.5 mm, and 69 mm) to line up with the user's interpupillary distance to ensure image clarity and allow for a more immersive experience (45). The PN3P is also suitable for a wide range of head shapes and facial features, as it uses an adjustable rear strap and polyurethane leather foam face cushion to properly position the VR device on the user's face (45). The all-hygienic materials of the P3NP make the VR headset easy to clean and ideal to share between multiple users (45). It is ergonomically designed for users to comfortably wear for long periods of time by counterbalancing the weight of the front display with the rear battery (44). The total weight of the PN3P is 673 g (46), which is in the middle range for other 4k standalone VR headsets with similar specifications and release date, such as the Oculus Quest 2 at 503 g (47) and HTC Vive Focus 3 at 785 g (48). Non-standalone (tethered) VR headsets require a cable connection to a personal computer (PC) to run the VR software, which increases the weight of the VR headset, restricts user mobility, and can be cumbersome for cable management. Tethered VR headsets also increase the complexity in setup for users and have additional costly and bulky hardware requirements (PC, graphics card, etc.), thus making a standalone system the preferred choice for a home-based VRGM intervention.

### Feasibility evaluation

2.6

A log containing information on the number of patients approached for participation, the number referred to the research team, the number successfully contacted by the research team, and those who consented will be maintained. The number of patients who declined or did not meet the eligibility criteria and the underlying reasons will also be recorded. Another log will be maintained for the number of participants who dropped out during the study. Home practice will be tracked through engagement data from the VR device, which include session length, total time spent using the headset, and number of daily VRGM sessions. Data collected from the VR device will be verified through a daily home practice log. The log will provide space to input the date, number of VRGM sessions completed each day, total number of minutes per session, and comments about their experience and side effects. Participants will also be contacted once weekly to ask whether they have experienced any side effects. Data obtained from study logs will be used to calculate recruitment and study completion rates. Data collected from the VR system, home practice logs, and weekly emails will be used to evaluate intervention adherence and safety.

### Outcome measures

2.7

All the study measures are described in Table 4 (51–65). Standardized measures of pain, sleep, depressive and anxiety symptoms, fatigue, and quality of life (objective 2), as well as trait mindfulness and levels of immersion and presence in the VR experience (objective 3), will be used. Sociodemographic and medical information collected from participants at baseline will include age, sex, gender, race and ethnicity, cancer type and stage, time since diagnosis, time since last treatment, presence and severity of comorbidities, educational level, marital status, occupational status, and type and frequency of nonpharmacological interventions used for pain in the last 3 months. The prescribed analgesic regimen (standing and as needed) will also be obtained. This will include the number of analgesics prescribed, types of analgesics, frequency of administration, route of administration, and prescribed dose. The entire battery of questionnaires has been user-tested and requires approximately 30 min to complete.

**Table 4 T4:** Outcome measures.

Construct	Measure	Description
Pain		
Pain intensity	Numeric pain rating scale (51, 52)	0–10 Likert Scale (0: no pain at all; 10: worst possible pain); widely used and validated in oncology (51, 52)
Pain severity and interference	Pain questionnaire (53, 54)	7-item scale that assesses pain frequency, location, duration, intensity, and emotional upset due to pain in the past 7 days. This scale has demonstrated good validity and reliability coefficients (53, 54).
Pain catastrophizing	Pain catastrophizing scale (55)	13-item questionnaire that assesses on a 5-point scale, ranging from 0 (not at all) to 4 (always), to which degree one experiences certain thoughts or feelings during pain over the past 7 days. Studies have supported the psychometrics of this scale (55).
Neuropathic pain quality	PROMIS^a^ Neuropathic Pain Quality (56)	5-item scale that assesses neuropathic pain over the past 7 days; used to distinguish between neuropathic and non-neuropathic pain conditions. PROMIS-Pain Quality-Neuro has demonstrated good psychometric properties (Cronbach's alpha = 0.87) (56).
Pain interference	PROMIS-SF^b^-8a-pain interference (57)	8-item scale that assesses pain interference with function in the past 7 days. Items are scored on a 1–5 scale. Alpha reliability ranges from .96 to .99 and construct validity (57).
Analgesic use	Investigator-developed	Daily analgesic use log including the name, dosage, and frequency of all pain medications.
Virtual reality experience		
Immersion	1–10 likert scale add-on to the immersive experience questionnaire (IEQ) (58)	One 1–10 Likert scale that rates how immersed did a participant feel during VR (1 = not at all immersed, 10 = very immersed). The psychometrics of the IEQ questionnaire has been evaluated in a general population study of 260 participants with high reliability and validity coefficients (58).
Presence	Slater-usoh-steed (SUS) questionnaire (59)	3-item 1–7 Likert-scale questionnaire that evaluates presence (i.e., the sense of being in a VR; the extent to which a VR feels real; and the extent to which a VR is thought of as a place visited). The SUS questionnaire has demonstrated good psychometric properties in various populations with well-established concurrent validity with other measures of VR presence (59).
Sleep		
Sleep quality	Pittsburgh sleep quality index (PSQI) (60)	PSQI includes 19 items grouped into 7 subscales: (1) sleep quality, (2) sleep efficiency, (3) daytime dysfunction, (4) sleep latency, (5) sleep disturbances, (6) sleep duration, and (7) use of sleep medication. Items are scored on a 0–3 scale. PSQI has demonstrated adequate reliability and validity among cancer patients, with Alpha reliability coefficients ranging from .70 to .80 (60).
Sleep amount and quality, pain interference with sleep	Sleep diary (61)	A sleep diary that is well-validated for use with chronic pain patients. It assesses one's previous night's sleep, including the number of hours slept, sleep onset latency, number of awakenings, sleep quality (Likert scale; 0 = “extremely poor” to 5 = “extremely good”), and sleep restfulness (Likert scale; 0 = “not at all rested” to 5 = “well rested”) (61), as well as one's level of pain at bedtime and upon awakening on a 6-point Likert scale (0: no pain at all; 5: very intense pain) (61, 62)
Depression and anxiety symptoms		
Anxiety	PROMIS-SF-8a-anxiety (63)	8-item scale that measures anxiety over the past 7 days. Items are scored on a 1–5 scale. PROMIS-SF-anxiety scale has shown excellent convergent and discriminate validity with other measures, with a Cronbach's alpha of .95 (63).
Depression	PROMIS-SF-8a-depression (63)	8-item questionnaire that assesses depression over the past 7 days. Items are scored on a 1–5 scale. The PROMIS-SF-depression has demonstrated good validity and reliability coefficients (Cronbach's alpha = .91) (63).
Fatigue		
Fatigue	PROMIS-SF-8a-fatigue (63)	8-item scale that measures fatigue over the past 7 days. Items are scored on a 1–5 scale. PROMIS-SF-fatigue has demonstrated good psychometric properties with reliability coefficients ranging from .72 to .88 and concurrent validity with other measures of fatigue, ranging from 0.6 to 0.85 (63).
Trait mindfulness		
Trait mindfulness	Five-facet mindfulness questionnaire short form (FFMQSF) (64)	15-item measure of trait mindfulness with five subscales: non-reactivity to inner experience, observing sensations, acting with awareness, describing with words, and non-judging of experience. Items are scored on a 1–5 scale. The FFMQSF is widely used in oncology with sound psychometrics (64).
Quality of life		
Overall health and QOL	Two items add-on to the EORTC QLQ-C30^c^ (65)	Two 1–7 likert scales add-on to the EORTC QLQ-C30 that rates self-perceived health and QOL during the last 7 days. EORTC QLQ-C30 has been well validated in oncology (65).

^a^
PROMIS, patient-reported outcomes measurement information system.

^b^
PROMIS-SF, patient-reported outcomes measurement information system-short form.

^c^
EORTC QLQ-C30, European organization for the research and treatment of cancer (EORTC) quality of life questionnaire; QOL, quality of life.

### Timing of assessments

2.8

Timing of assessments is fully described in Table 5 (schedule of measures).

**Table 5 T5:** Schedule of measures.

		Treatment and follow-up							
	Enrollment	Baseline	1 week	2 weeks	3 weeks	4 weeks	5 weeks	6 weeks	12 weeks
Education and consent	X								
Screening checklist	X								
Demographic questionnaire and medication history	X								
Objective 1 (feasibility)									
Home practice log			D^a^	D	D	D	D	D	
Objectives 2 and 3 (benefits and factors)									
Pain Numeric rating scale (scores 0–10)^b^			D	D	D	D	D	D	
Immersive Experience Questionnaire^b^			D	D	D	D	D	D	
Slater-Usoh-Steed scale^b^			D	D	D	D	D	D	
Analgesic use log			D	D	D	D	D	D	
Sleep diary^c^		X						X	X
PROMIS^d^-Short form–pain interference scale		X	X	X	X	X	X	X	X
Pain questionnaire		X						X	X
Pain catastrophizing scale		X						X	X
PROMIS neuropathic pain quality		X						X	X
Pittsburgh sleep quality index		X						X	X
PROMIS-short form–anxiety scale (8a)		X						X	X
PROMIS-short form–depression scale (8a)		X						X	X
PROMIS-short form–fatigue scale (8a)		X						X	X
EORTC QLQ-C30^e^ (2 likert scales with scores of 0–10)		X						X	X
Five-facet mindfulness questionnaire–short form		X						X	X

^a^
D: daily completion over the course of the entire study through week 6.

^b^
Responses on the Pain Numeric Rating Scale, Immersive Experience Questionnaire, and Slater Usoh-Steed Scale are recorded using the virtual reality device.

^c^
Participants will maintain a sleep diary for 1 week at baseline, post intervention, and 6 weeks post intervention (12 weeks).

^d^
PROMIS, patient-reported outcomes measurement information system.

^e^
EORTC QLQ-C30, European organization for the research and treatment of cancer quality of life questionnaire.

#### Objective 2

2.8.1

Psychosocial outcome measures (i.e., pain, sleep, fatigue, depressive and anxiety symptoms, and quality of life) will be assessed before and after the intervention and 6 weeks post intervention (follow-up). As noted above, pain-related functional impairment is often a priority in chronic pain mitigation efforts and is thus an important outcome for this feasibility trial. Therefore, pain interference with function will be assessed weekly during the 6-week intervention period and then again at follow-up. The VR device will record the intensity of participants’ pain on a Numeric Rating Scale (scores of 0–10) (51) before and immediately after each VRGM session. Participants will maintain analgesic use in the home practice logs to record their use of pain medications and dosages daily, until completion of the 6-week VRGM intervention. Additionally, they will maintain a sleep diary for 1 week before and after the intervention, as well as at 6 weeks post intervention (follow-up), including assessments of sleep duration and quality and pain interference with sleep. Since sleep diaries evaluate sleep on a daily basis, many of the limitations of retrospective self-reported sleep measures are minimized, such as recall bias and recency bias (tendency to recall last few nights) (66).

#### Objective 3

2.8.2

The VR device will record participants’ level of immersion and presence in each VRGM session. Trait mindfulness will be evaluated before and after the intervention and 6 weeks post intervention (follow-up).

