#### Objective 1: to evaluate the feasibility of a self-administered, at-home, 6-week VRGM program for chronic CRP

1.2.1

Feasibility outcomes include recruitment rates, intervention adherence, and study completion rates, as well as intervention safety as determined by the occurrence, type, and severity of negative side effects.

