#### Sample size

2.2.1

This protocol is designed as a mixed methods feasibility study. The recruitment goal is 15 participants, a sample which is comparable to other mindfulness studies primarily focusing on feasibility, reporting sample sizes of 13–19 participants (39, 40). This sample size can allow the evaluation of feasibility outcomes by providing crucial information about the ability to recruit this population to such an intervention, intervention safety, adherence, and study completion rates. Feasibility will also partly be determined by participants’ attitudes toward VRGM and level of satisfaction with the intervention during the semistructured interviews.

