#### Quantitative analysis

2.9.1

Descriptive statistics will be used to calculate accrual rates (and reasons for not consenting to the trial), retention in the trial, intervention adherence, questionnaire completion, and adverse event rates (objective 1). Means and SDs will be calculated for continuous variables and frequency distributions for categorical variables. The profile of each outcome (means and SDs) will be displayed to visualize the pattern of changes over time (objective 2). Effect sizes and confidence intervals of changes in scores for outcome measures (i.e., pain, sleep, fatigue, depressive and anxiety symptoms, and quality of life) will be described across different time points (objective 2). Exploratory analyses will be used to describe the strength of associations of pre- to post-VRGM pain changes with the levels of immersion and presence in the VR experience, total amount of VRGM practice, and change in pre- to post-VRGM trait mindfulness (objective 3).

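### Headset pain ratings taken before and after each session are not clearly part of the primary safety evaluation, and no count of participants or sessions with a rise in pain is planned

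*Protocol article*

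**What the plan says.** All references are to the protocol article.

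- **Measurement.** Section 2.8.1 has the VR device record pain intensity (0–10) "before and immediately after each VRGM session". Footnote b of Table 5 confirms that the device captures this scale.
- **Assignment.** Table 5 lists the scale under the block "Objectives 2 and 3 (benefits and factors"). The Objective 1 block contains only the home practice log.
- **Analysis of outcomes.** Section 2.9.1 states: "The profile of each outcome (means and SDs) will be displayed to visualize the pattern of changes over time (objective 2"). It adds effect sizes and confidence intervals of change, and for Objective 3 the strength of association between pain change and immersion, presence, practice and trait mindfulness.
- **Safety.** Section 1.2.1 places safety in the primary objective: "intervention safety as determined by the occurrence, type, and severity of negative side effects". Section 2.9.1 analyses it as adverse event rates.
- **Safety sources.** Section 2.6 says: "Data collected from the VR system, home practice logs, and weekly emails will be used to evaluate intervention adherence and safety". The device data described in that section are for adherence (the list closes with a session count): "Home practice will be tracked through engagement data from the VR device, which include session length, total time spent using the headset, and number of". The log has room for comments on side effects, and a weekly contact asks about them.

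**The concern.** The trial holds a graded symptom record taken on both sides of every session, and the article does not say whether the safety evaluation uses it. The routes it does describe for side effects are log comments and a weekly question, and both depend on the participant regarding the event as a side effect. Every participant enters with cancer-related pain of more than three months and pain interference above 3 (Table 1). A temporary increase in a familiar symptom may not be reported under that label. Some Table 3 exercises direct attention to pain or to the body, so a rise in some sessions is at least plausible.

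Means, SDs and effect sizes do not show how many people got worse. The trial could report a favourable mean change and a low side-effect rate while a minority repeatedly ended sessions with more pain. It could also leave unexamined whether rises cluster in particular exercises. Both matter because section 3.1 presents this study as the foundation for a larger one.

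**Working it through.** **Inputs from the article.** The recruitment goal is 15 (section 2.2.1), set by precedent: "The recruitment goal is 15 participants, a sample which is comparable to other mindfulness studies primarily focusing on feasibility". The dose of practice is given in section 2.4: "the VRGM intervention will consist of a 10–15 min, once-daily session for 6 weeks". There is no alpha, power, effect size or safety threshold, so the plan has no calculated figure to reproduce.

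**Step 1: data available at full adherence.**
- Sessions per participant: 6 × 7 = 42.
- Paired ratings in total: 15 × 42 = 630.
- Paired ratings per Table 3 exercise, if the seven-day cycle repeats weekly: 630 / 7 = 90.

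**Step 2: can the planned summaries hide a worsening minority?** The changes below are assumed, with one average within-session change per participant. With k of 15 worsening by u and the rest changing by d, the mean is [k·u + (15 − k)·d] / 15, and the 95% CI is the mean ± t(0.975; 14) × SD / √15.

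| Worsening | Changes assumed | Mean | SD | 95% CI |
|---|---|---|---|---|
| 2/15 (13%) | +2, −1.5 | −1.03 | 1.23 | −1.72 to −0.35 |
| 3/15 (20%) | +2, −1.5 | −0.80 | 1.45 | −1.60 to 0.00 |
| 3/15 (20%) | +2, −2 | −1.20 | 1.66 | −2.12 to −0.28 |
| 5/15 (33%) | +2, −1.5 | −0.33 | 1.71 | −1.28 to 0.61 |

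The second row in full: (3 × 2 + 12 × (−1.5)) / 15 = (6 − 18) / 15 = −0.80. The SD is √[(12 × 0.7² + 3 × 2.8²) / 14] = √(29.4 / 14) = 1.45.

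With 13% to 20% worsening, the mean still indicates benefit. With a third worsening, the masking largely disappears. The SD signals spread but does not say how many participants rose.

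**Step 3: what a count of participants would offer.** Exact (Clopper–Pearson) 95% intervals are 0% to 21.8% for 0/15, 0.2% to 31.9% for 1/15 and 4.3% to 48.1% for 3/15. The chance of seeing at least one such participant is 1 − (1 − p)^15, which is 54%, 79% and 96% for assumed true rates of 5%, 10% and 20%. The count is imprecise but informative. The 630 sessions are clustered within participants, so a simple binomial interval on sessions would be too narrow.

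**Step 4: should repeated rises be counted automatically as side effects?** Assume that 5% of sessions show a qualifying rise by chance, independently. The probability of two or more in 42 sessions is 1 − 0.95^42 − 42 × 0.05 × 0.95^41 = 1 − 0.116 − 0.256 = 0.63. About 63% of participants would be labelled from noise alone, so such a rule would distort the primary outcome.

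**The case against.** The strongest reply is that section 2.6 already names VR-system data as a source for safety, and the pain ratings are VR-system data. The usage measures listed there describe how home practice is tracked and do not limit the safety sentence. This stands in part. The ratings are not excluded, but they are not named either, and Table 5 places them under other objectives.

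A reader might infer that the ratings serve only as a benefit measure and that the safety result is bound to miss a harm. The documents do not support that. Pain change is also used for Objective 3. Nothing bars worse pain from being recorded as a side effect in the daily log or at the weekly contact, which asks directly. Worsening could also surface in the weekly pain-interference scale, the analgesic log or the interviews, which are offered to dropouts too.

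It is also fair to say that no passage reports that attending to pain raises it. The background describes reductions, and simulator sickness is the only specific VR side effect named. The rise is therefore a plausible event, not a documented one. The illustrated changes are assumed, and the planned SDs and confidence intervals would show some of the spread.

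Finally, counts above a margin are often left to a fuller protocol or an analysis plan, which is not shown here. That limits the point to a clarification and a small addition. It does not remove the unclear relation between section 2.6 and Table 5.

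**Conclusion.** The point holds in limited form. The article leaves unclear whether device-recorded pain ratings enter the primary safety evaluation, and the summaries it states for them cannot show how many participants or sessions worsened. The safety evaluation may therefore miss within-session worsening that is not reported as a side effect. It cannot be said that it will.

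The size depends on assumed changes. With 2 or 3 of 15 participants worsening by 2 points and the rest improving by 1.5, the mean change is −1.03 or −0.80. No sample size or other stated figure is affected. Because safety is part of the primary objective and the data are already collected, this is a worthwhile low-cost improvement and not a flaw in the design.

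**What to change.** - In section 2.6, state that the pain ratings taken by the headset before and after each session feed the Objective 1 safety evaluation, and align Table 5 with this.
- In section 2.9.1, report beside the mean change the number and percentage of participants, and of sessions, with a post-session rating above the pre-session rating. Give any rise, and a rise above a margin that the investigators fix in advance, overall and by Table 3 exercise.
- Present these counts separately from the self-reported side-effect or adverse event rate, and do not reclassify anyone automatically as having had a side effect.
- Note that without a control arm some rises will be natural fluctuation and cannot be attributed to the intervention.

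The cost is a few lines of text and one descriptive table from data the headset already captures. The safety picture may look less favourable, and the counts by exercise will be small and should be read only as description.

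### The 0–10 pain NRS is taken only around VR sessions, so it has no scheduled out-of-session baseline, post-intervention or 12-week rating, and its course over the weeks depends on who practised

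*Protocol article*

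**What the plan says.** Table 4 names the NRS against the construct of pain intensity. Section 2.8.1 (Objective 2) has the VR device record it "before and immediately after each VRGM session". Footnote b of Table 5 confirms the route: "Responses on the Pain Numeric Rating Scale, Immersive Experience Questionnaire, and Slater Usoh-Steed Scale are recorded using the virtual reality device". No paper or web version of the scale is described.

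In Table 5 the NRS row carries D in weeks 1 to 6 and nothing at Baseline or 12 weeks. Footnote a defines D as "daily completion over the course of the entire study through week 6". The table is offered as the complete schedule: "Timing of assessments is fully described in Table 5 (schedule of measures".

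Section 2.8.1 says of the psychosocial outcomes, pain among them, that they "will be assessed before and after the intervention and 6 weeks post intervention (follow-up". Section 2.9.1 then plans that "The profile of each outcome (means and SDs) will be displayed to visualize the pattern of changes over time", together with effect sizes of change. It also plans exploratory associations between pain change and, among other factors, the total amount of practice (Objective 3).

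**The concern.** A rating that exists only when a session is held is observed selectively. If participants skip the headset when pain is bad, or stop using it for that reason, the mean of the observed ratings falls over six weeks although nobody has improved. If they use it more on bad days, a real benefit can be masked. The intended schedule is a "10–15 min, once-daily session for 6 weeks", but adherence to it is itself a primary feasibility outcome, so full practice cannot be assumed.

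Two planned descriptions are exposed. One is the NRS profile and change over weeks under Objective 2. The other is any use of the NRS under Objective 3, where the availability of the pain measure would depend on the same practice variable it is being related to. The study is meant to lay the foundation for a larger efficacy study, so the measurement scheme may be carried forward.

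**Working it through.** **1. Schedule, measure by measure (Tables 4 and 5, section 2.8.1)**

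| Measure | Baseline | During weeks 1–6 | 6 weeks | 12 weeks | Needs a VR session? |
|---|---|---|---|---|---|
| NRS 0–10 | none | before and after each session | in-session only | none | yes |
| Pain questionnaire (7-day recall, includes intensity) | yes | no | yes | yes | no |
| Sleep diary, pain 0–5 at bedtime and on waking (1 week each time) | yes | no | yes | yes | no |
| PROMIS pain interference | yes | weekly | yes | yes | no |

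Footnote a (every day) and footnote b (recorded in the headset) agree only if every participant practises every day.

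**2. Number of NRS ratings**

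One session a day for 6 × 7 = 42 days, two ratings each, gives 84 per participant and 15 × 84 = 1,260 in all. At 80%, 60% and 40% of sessions held this becomes 1,008, 756 and 504. Scheduled ratings at Baseline, at 12 weeks and on any skipped day: zero.

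The earliest rating is the one before the first home session. It precedes the home programme, but it is a single momentary value, it follows the 15 min trial session of section 2.3.2, and it is not scheduled as Baseline.

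**3. How far the profile could move with no true change**

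The article states no figure to reproduce; it gives no SD, adherence rate or link between pain and practice. All inputs here are assumptions:

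- daily NRS = 5 + person effect (SD 1.5) + day effect (SD 1.5), constant over time;
- log-odds of holding a session = b + s × (NRS − 5), with s = −0.3 or −0.4, so the odds per NRS point are multiplied by exp(−0.3) = 0.74 or exp(−0.4) = 0.67, that is, 26% or 33% lower;
- b chosen so that practice is 80% or 95% in week 1, and 60% (s = −0.3) or 50% (s = −0.4) in week 6.

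| s | Practice, week 1 → week 6 | Observed mean, week 1 → week 6 | Pooled change | Within-person change |
|---|---|---|---|---|
| −0.3 | 80% → 60% | 4.75 → 4.50 | −0.24 | −0.13 |
| −0.3 | 95% → 60% | 4.93 → 4.51 | −0.42 | −0.22 |
| −0.4 | 80% → 50% | 4.67 → 4.22 | −0.45 | −0.24 |
| −0.4 | 95% → 50% | 4.91 → 4.22 | −0.69 | −0.37 |

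Changes are computed before rounding. The within-person change is averaged over people with at least one rating in both weeks. With s = 0 the change is 0. With s = +0.3 or +0.4 the sizes are the same to within 0.01 and the sign is positive.

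The right comparison for a fall over time is observed week 6 against observed week 1. Setting observed week 6 against the true mean of 5 would give 0.5–0.8, which overstates the fall because week 1 is already selected in the same direction.

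**4. Sensitivity to other assumptions**

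With week-1 practice at 95% and odds ratios from 0.6 to 1.67 per point, the pooled false change runs to these limits:

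| Week-6 practice | Between/within-person SD 1.5/1.0 | SD 2.0/1.5 |
|---|---|---|
| 80% | ±0.21 | ±0.37 |
| 60% | about ±0.49 | about ±0.84 |
| 40% | ±0.77 | about ±1.33 |

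**The case against.** The best defence is that paired ratings around each session are the right design for acute within-session change, and that no section names the NRS as the measure of change from baseline to follow-up. Section 2.9.1 speaks of pain without naming an instrument, and how the NRS is to be aggregated may be set out in an analysis plan not shown. The study has 15 participants and one arm, is descriptive, and disclaims power for efficacy. Practice is logged daily, so the missing days can at least be identified. All of this stands, and it limits the consequence. It does not remove the point: the text plans a time profile for each outcome, and no later analysis can supply ratings that were never collected.

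A reader might infer three stronger things that the article does not support.

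- *That there is no NRS value before the intervention.* The rating before the first home session is one, though a weak one.
- *That pain-intensity change cannot be reported, or that section 2.8.1 contradicts Table 5.* The statement in section 2.8.1 concerns pain as a domain, and several instruments meet it independently of sessions. Change on the Pain questionnaire needs only its own baseline, which it has.
- *That a bias of known size and direction is present.* No document gives the inputs, and the sign is unknown.

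**Conclusion.** The point holds for this scale, not for pain intensity as a construct. The NRS has no scheduled rating outside sessions at baseline, post intervention or 12 weeks, and none on days without a session, despite the daily label in Table 5. Its profile across weeks, and any use of it against amount of practice, therefore depends on who practised and when. No NRS change to 12 weeks can be reported, and change from before the programme would rest on one momentary rating per person.

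Under the assumptions in step 3 of the working, the false week 1 to week 6 change is about 0.2–0.7 points in pooled means and 0.1–0.4 within person. That range is illustrative: steeper links or lower adherence widen it, and no link makes it zero. Within-session change remains measurable for the sessions held.

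**What to change.** Add one 0–10 NRS item, asked at a fixed time of day, to the daily home practice log, to be completed whether or not the headset is used. Add the same item to the three 1-week sleep-diary periods (baseline, post intervention, 12 weeks). Enter the Baseline and 12-week cells in the NRS row of Table 5, and show the log and diary rating separately from the in-headset rating. State that NRS change over time under Objective 2 uses the log and diary ratings, and that the in-headset ratings serve within-session change only.

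If the item is not added, restrict the NRS to within-session change, use the Pain questionnaire intensity item for change to weeks 6 and 12, and reword footnote a for this row so that it says per session held.

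The cost is one item on forms already in use, a table edit, and seconds of extra burden per day.
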